## Abstract

**Background:**

Individuals receiving long-term oxygen therapy (LTOT) are often confined to their homes and have impaired health-related quality of life (HRQoL). Despite technological advances, monitoring these individuals remains a challenge.

**Objective:**

This study aims to evaluate the impact of remote monitoring on HRQoL, dyspnea, health status, symptoms of anxiety and depression, and adherence to data entry via a mobile app in individuals receiving LTOT.

**Methods:**

This randomized controlled trial will recruit 60 participants, including clinically stable adults diagnosed with chronic obstructive pulmonary disease (COPD) or interstitial lung disease (ILD) who use LTOT. Participants will be randomized in a 1:1 ratio to either the control group (CG) or the intervention group (IG), stratified by diagnosis (COPD or ILD), and will be followed for 90 days. All participants will use a mobile app that serves as the central platform for remote monitoring. The app enables daily recording of physiological data, including heart rate (HR), peripheral oxygen saturation (SpO_2_), and oxygen flow rate. In addition, validated questionnaires (EQ-5D-5L, modified Medical Research Council [mMRC] Dyspnea Scale, Hospital Anxiety and Depression Scale [HADS], and COPD Assessment Test [CAT] or the King Brief Interstitial Lung Disease [K-BILD] questionnaire, depending on diagnosis) will be self-administered through the app at predefined time points. The CG will receive monthly telephone follow-up (every 30 days), while the IG will receive biweekly telephone follow-up (every 15 days). During these structured calls, trained health care professionals will collect clinical information and ensure data completeness. In addition, participants in the IG will use a wearable smartwatch that enables continuous physiological monitoring (HR and SpO_2_), with data transmitted to a secure platform and analyzed weekly using an AI-assisted system to support adherence monitoring and identify physiological patterns. Participants in the IG may receive additional contact if clinically relevant abnormalities or reduced adherence are detected. Outcomes will be interpreted according to the minimal clinically important difference (MCID) for dyspnea (mMRC Dyspnea Scale), health status (CAT or K-BILD), quality of life (EQ-5D-5L), and psychological symptoms (HADS).

**Results:**

Funding and ethics approval were obtained in April 2023. Recruitment began in January 2024 and was completed in May 2026. A total of 62 participants were randomized, of whom 60 initiated follow-up and were included in the longitudinal analysis. Overall, 49 participants completed the 90-day follow-up. Data collection has been completed, and data analysis is ongoing. The results are expected to be submitted for publication in the first half of 2027.

**Conclusions:**

This study will provide relevant evidence on the effect of remote monitoring in individuals receiving LTOT on HRQoL, dyspnea, health status, anxiety and depression, and engagement with data entry through a mobile app.

**Trial Registration:**

ClinicalTrials.gov NCT06882265; https://clinicaltrials.gov/study/NCT06882265

## Introduction

Hypoxemia is common in individuals with respiratory diseases and can represent a potentially harmful physiological impairment associated with adverse outcomes [1]. Additionally, individuals with hypoxemia often experience persistent dyspnea, reduced physical activity, and social isolation [2], leading to impaired health-related quality of life (HRQoL) [3]. Long-term oxygen therapy (LTOT) is recommended for chronic hypoxemia and involves administering oxygen for at least 15 hours per day.

According to clinical guidelines, LTOT is indicated for patients with chronic respiratory diseases [4]. LTOT has positive effects on fatigue, sleep quality, and physical activity and increases survival time [5]. Despite these benefits, managing LTOT remains challenging due to the need to monitor correct oxygen use, adjust the oxygen dose based on clinical progression, address device-related limitations, and ensure patient adherence to therapy [5-7]. These challenges highlight opportunities to improve and optimize monitoring strategies and have driven interest in remote monitoring technologies as a promising approach to support patients receiving LTOT.

Remote monitoring can allow continuous or periodic tracking of oxygen saturation, respiratory rate, and patient activity levels. These data may support clinical decision-making and enhance patient management [8]. However, few studies have evaluated the clinical outcomes of remote monitoring specifically in patients receiving LTOT, highlighting the need for further research in this population [9-11]. Furthermore, we hypothesize that remote monitoring would improve the quality of life of patients receiving LTOT.

This study aims to evaluate the impact of remote monitoring with wearable devices on HRQoL in individuals receiving LTOT. The secondary aim is to assess the effects of remote monitoring on psychosocial status, dyspnea severity, and adherence to data entry via a mobile app.

## Methods

### Participants

Individuals of either sex aged 18 to 85 years with chronic hypoxemia due to chronic obstructive pulmonary disease (COPD) or interstitial lung disease (ILD) will be eligible if they have been receiving LTOT for at least 6 months, are receiving optimized pharmacological treatment, and have had no exacerbations during the preceding 2 months. They also need to own a smartphone compatible with the app that monitors quality of life and vital signs. Exclusion criteria will include cognitive or other limitations that impair the understanding of questionnaires, residence outside the metropolitan area where the hospital is located, and inability to use a smartphone or use of a device with an operating system other than iOS or Android. Participants will be screened and recruited at the pulmonology outpatient clinic of a tertiary university hospital. Enrollment in the study will occur after the informed consent form is signed. The schedule of enrollment, allocation, interventions, and assessments is outlined in Table 1.

**Table 1 table1:** Schedule of study assessments and data collection during the 90-day follow-up period.

Assessments	Screening	Baseline (day 0)	Day 15	Day 30	Day 45	Day 60	Day 75	Day 90
Eligibility screening	✓							
Informed consent	✓							
Randomization		✓						
Mobile app installation and training		✓						
Control group telephone follow-up				✓		✓		✓
Intervention group telephone follow-up			✓	✓	✓	✓	✓	✓
Wearable monitoring (intervention group)		✓	✓	✓	✓	✓	✓	✓
Daily physiological data entry via the mobile app^a^		✓	✓	✓	✓	✓	✓	✓
EQ-5D-5L		✓		✓		✓		✓
Hospital Anxiety and Depression Scale		✓		✓		✓		✓
Modified Medical Research Council Dyspnea Scale		✓		✓		✓		✓
COPD Assessment Test or King Brief Interstitial Lung Disease questionnaire		✓		✓		✓		✓

^a^Participants are instructed to enter physiological data into the mobile app daily throughout the follow-up period.

### Study Design

This randomized, controlled, 2-arm, assessor-blinded clinical trial protocol was approved by the Hospital das Clínicas, University of São Paulo Medical School research ethics committee (6.012.012) and registered at ClinicalTrials.gov (NCT06882265). Adults receiving LTOT will be invited to participate in the study after a pulmonology outpatient consultation. Participants will be assessed and followed for 90 days. At the initial visit, all participants will undergo the following assessments: anthropometric measurements (weight and height) and clinical characteristics, including the number of exacerbations during the 6 months prior to randomization, respiratory symptoms, medication use, and daily oxygen therapy use and prescription. Patients were not involved in the design, conduct, reporting, or dissemination plans of this study. The study protocol was developed in accordance with the SPIRIT (Standard Protocol Items: Recommendations for Interventional Trials) checklist guidelines [12], and the study design is presented in Figure 1.

**Figure 1 figure1:**
[figure not shown]
Study design. AI: artificial intelligence; APP: application; CAT: COPD Assessment Test; CG: control group; COPD: chronic obstructive pulmonary disease; HADS: Hospital Anxiety and Depression Scale; HR: heart rate; IG: intervention group; ILD: interstitial lung disease; K-BILD: King Brief Interstitial Lung Disease questionnaire; LTOT: long-term oxygen therapy; mMRC: modified Medical Research Council Dyspnea Scale; QoL: quality of life; SpO₂: peripheral oxygen saturation.

### Mobile App and Baseline Assessments

A study-specific mobile app will be installed on participants’ smartphones and used as the central platform for remote monitoring. The app allows daily recording of physiological data, including heart rate (HR), peripheral oxygen saturation (SpO_2_), and oxygen flow rate. In addition, validated questionnaires (EQ-5D-5L, modified Medical Research Council [mMRC] Dyspnea Scale, Hospital Anxiety and Depression Scale [HADS], and COPD Assessment Test [CAT] or King Brief Interstitial Lung Disease [K-BILD] questionnaire, depending on diagnosis) will be self-administered through the app at predefined time points during follow-up. At baseline, all participants will complete the same standardized questionnaires through the app prior to randomization.

All participants will receive standardized training on the use of the pulse oximeter and the mobile app, as well as a written instruction manual. Participants in the intervention group (IG) will also receive detailed guidance on synchronizing the wearable device with the smartphone app.

### Randomization and Blinding

Participants will be randomized in a 1:1 ratio to either the control group (CG) or the IG. The randomization sequence will be generated using an online randomizer (Sealed Envelope; Sealed Envelope Ltd) by an investigator who is not involved in patient recruitment, assessment, or intervention and who will perform the group allocation. Group allocation will be concealed using consecutively numbered, sealed, opaque envelopes. Randomization will be stratified by diagnosis (ILD or COPD).

### Interventions

#### Control Group

Participants in the CG will receive a pulse oximeter (Morya, model AS304) and will be followed for 90 days. They will receive monthly telephone follow-up every 30 days. During these structured calls, a trained health care professional will collect clinical information, including exacerbations, respiratory symptoms (cough, dyspnea, and shortness of breath), medication adherence, and oxygen use. All study questionnaires (EQ-5D-5L, mMRC Dyspnea Scale, HADS, and CAT or K-BILD, depending on diagnosis) will be self-administered by participants through the mobile app at predefined time points (baseline, day 30, day 60, and day 90). During scheduled telephone follow-up calls, health care professionals will reinforce questionnaire completion, collect clinical information (exacerbations, respiratory symptoms, medication adherence, and oxygen use), and provide support as needed. HR and SpO_2_ will also be recorded using the pulse oximeter on the day of follow-up. Participants will continue using the mobile app for daily recording of physiological data.

#### Intervention Group

Participants in the IG will receive a pulse oximeter and the Garmin Ltd Venu SQ Smartwatch (Garmin International Inc; 2020 wearable monitor). The wearable device will be synchronized with the mobile app, enabling the continuous transmission of HR and SpO_2_ data to a secure cloud-based platform. Oxygen flow rate will be entered by participants through the mobile app.

The IG will receive biweekly telephone follow-up every 15 days. All study questionnaires (EQ-5D-5L, mMRC Dyspnea Scale, HADS, and CAT or K-BILD, depending on diagnosis) will be self-administered by participants through the mobile app at predefined time points (baseline, day 30, day 60, and day 90). During the scheduled telephone follow-up calls, health care professionals will reinforce questionnaire completion, collect clinical information (exacerbations, respiratory symptoms, medication adherence, and oxygen use), and provide support as needed. In addition, wearable-derived data will be monitored weekly by the research team and analyzed using an AI-assisted system designed to identify physiological patterns and support adherence monitoring. The system does not perform autonomous clinical decision-making; all alerts are reviewed by health care professionals prior to any clinical action.

The remote monitoring platform includes an automated data analysis system designed to support adherence monitoring and the identification of abnormal physiological patterns. The system analyzes daily patient-entered data and wearable device data, including HR, SpO_2_, oxygen flow, and the frequency of data entry. The automated analysis system applies predefined rules based on individual baseline values established during the first 7 days of monitoring. Alert criteria include (1) sustained SpO_2_ reduction of ≥4% below the individual baseline; (2) sustained HR variation of 20 beats per minute more or less than the individual baseline; and (3) absence of data entry for 2 consecutive days, defined as low adherence. When any of these criteria are met, the system generates an alert. Although the platform automatically identifies predefined alert patterns, it does not perform autonomous clinical decision-making. All alerts are reviewed and interpreted by a trained health care professional within 24 hours before any participant contact or clinical recommendation. If the alert is confirmed as clinically relevant, the participant is contacted by telephone and, depending on the severity, advised to maintain self-care, contact their usual health care provider, or seek immediate medical evaluation. The remote monitoring system is intended to support patient monitoring and does not replace routine clinical care. Participants are also instructed to contact their usual health care provider whenever necessary.

Both groups receive enhanced standard care. However, the IG will receive continuous wearable-based physiological monitoring and more frequent follow-up, allowing the evaluation of the incremental benefit of remote monitoring beyond standard care. The primary purpose of these telephone contacts is data collection rather than active safety monitoring. However, any clinically relevant concerns identified during the calls will be appropriately addressed and, if necessary, escalated to ensure participant safety.

### Outcomes

#### Primary Outcome: HRQoL

The EuroQol questionnaire (EQ-5D-5L) is a tool used to assess HRQoL, comprising 1 question for each of the 5 dimensions: mobility, self-care, usual activities, pain or discomfort, and anxiety or depression. Responses can be converted into 3125 unique health states or converted into EQ-5D index values using an appropriate value set, typically anchored at 1 for perfect health and 0 for death, with possible negative values for health states considered worse than death. The EQ-5D questionnaire also includes a visual analog scale (VAS), through which respondents can report their perceived health status, with scores ranging from 0 (the worst possible health state) to 100 (the best possible health state). The minimal clinically important difference (MCID) for the EQ-5D-5L is not fixed and may vary according to baseline health status, population characteristics, and the type of intervention. Therefore, the interpretation of clinically meaningful change will consider context-specific estimates reported in the literature [13].

#### Secondary Outcomes

##### Anxiety and Depression Symptoms

The HADS will assess anxiety and depression symptoms. The questionnaire was developed to identify symptoms of anxiety and depressive mood and has been translated, validated, and published in Portuguese [14]. It consists of 14 multiple-choice questions divided into 2 subscales, HADS-anxiety (HADS-A) and HADS-depression (HADS-D), with 7 questions each. The domains are categorized by symptom severity: 0-7=“none,” 8-10=“probable,” and ≥11=“present” [15]. A change of 1.3 points in the anxiety domain and 1.5 points in the depression domain is considered the MCID [16].

##### Health Status

Health status in patients with COPD will be assessed using the CAT, a disease-specific questionnaire that evaluates the impact of symptoms on health status. It consists of 8 items related to health conditions and has been validated in several languages, including Portuguese [17]. A change of 2.0 points is considered the MCID [18].

Health status in patients with ILD will be assessed using the K-BILD questionnaire, a disease-specific instrument developed and validated for patients with ILD. It consists of 15 items that assess health status over the previous 2 weeks across 3 domains: psychological status, breathlessness and activities, and chest symptoms. The questionnaire is easy to administer and understand. Scores range from 0 to 100, with higher scores indicating better health status. A change of 5.4 points in the psychological domain, 4.4 points in the breathlessness domain, 3.9 points in the chest symptoms domain, and 3.9 points in the total score is considered the MCID [19]. The K-BILD has been translated and culturally adapted into Portuguese for use in Brazilian patients [20].

##### Dyspnea Symptoms

Dyspnea will be assessed using the mMRC Dyspnea Scale. It is a unidirectional scale ranging from 0 to 4 points that assesses daily activities that cause dyspnea [21]. A change of 1.0 point is considered the MCID [22].

##### Patient Adherence

Adherence will be assessed based on data entry into the mobile app. A participant will be considered adherent if data (HR, oxygen saturation, and oxygen flow) are entered for at least 30 of the 90 days of follow-up [23,24]. This threshold was defined to ensure a minimum level of engagement with the monitoring system while accounting for occasional missed entries.

### Statistical Analysis

The sample size calculation, based on the primary outcome of the study (EQ-5D-5L), was informed by a previous study reporting an observed difference of 0.04 in the EQ-5D-5L index, which was considered clinically meaningful within that specific study population [13]. This value was used as a pragmatic estimate of the expected effect size for sample size determination. The calculation was performed using G*Power software (*F* tests: ANOVA, repeated measures, within-between interaction). The calculation assumed an effect size of *f*=0.25, a 2-sided α level of .05, and a statistical power of 90% (β=.10). The design included 2 groups and 4 repeated measurements, with a correlation among repeated measures of 0.5 and a nonsphericity correction (ε) of 0.5. On the basis of these assumptions, the required sample size was 50 participants (25 per group), with an achieved power of 0.91. Considering an anticipated dropout rate of 20%, the final target sample size was increased to 30 participants per group to preserve statistical power under an intention-to-treat framework. The significance level will be set at 5% (*P*<.05) for all statistical tests, which will be conducted using GraphPad Prism (version 5.0; GraphPad Software LLC).

Data normality will be assessed using the Kolmogorov-Smirnov test, and homoscedasticity will be evaluated using the Levene test. Parametric data, defined by a normal distribution as demonstrated by histograms, will be presented as means and SDs (or SEs), while nonparametric variables will be presented as medians and IQRs.

Longitudinal outcomes will be analyzed using linear mixed-effects models with fixed effects for group, time, and group-by-time interaction and random intercepts for participants. The results will be interpreted in light of the established MCIDs for each outcome measure. Additionally, as a complementary analysis, the proportion of participants in each group achieving a within-individual change equal to or greater than the MCID will be calculated, providing a more clinically meaningful interpretation of the findings. Sensitivity analyses will be conducted to assess the robustness of the results.

The adherence criterion will be used in exploratory subgroup analyses to compare outcomes between adherent and nonadherent participants [25]. All primary longitudinal analyses will follow a modified intention-to-treat approach, including randomized participants who initiated follow-up and contributed data to the longitudinal analysis, regardless of adherence status. This approach preserves the benefits of randomization and reflects real-world conditions. Sensitivity analyses will be conducted to assess the robustness of the results.

For exploratory purposes, when appropriate, comparisons between groups at specific time points may be performed using parametric or nonparametric tests (eg, the *t* test or Mann-Whitney test), depending on data distribution. Pearson correlation coefficients will be used to assess associations between normally distributed variables, while Spearman correlation coefficients will be used for nonnormally distributed variables.

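### The 91% power belongs to f=0.25; nothing shown ties it to the 0.04 EQ-5D-5L difference named as the effect size, and it covers 0.04 only if the index SD is about 0.03 to 0.04

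*Protocol article*

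**What the plan says.** All of the sizing is in the Statistical Analysis section of the protocol article. It starts from "an observed difference of 0.04 in the EQ-5D-5L index, which was considered clinically meaningful within that specific study population" and continues: "This value was used as a pragmatic estimate of the expected effect size for sample size determination". G*Power was then run for a repeated-measures ANOVA, within-between interaction, with f=0.25, α=.05 and 90% power. The remaining inputs are: "The design included 2 groups and 4 repeated measurements, with a correlation among repeated measures of 0.5 and a nonsphericity correction (ε) of 0.5". The result is that "the required sample size was 50 participants (25 per group), with an achieved power of 0.91". Allowing for 20% dropout, the target became 30 per group.

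Three other places bear on the point:
- The primary outcome section describes an index anchored at 1 and 0 with negative values possible, and says that its MCID is not fixed.
- The Results section reports 60 participants in the longitudinal analysis and 49 completers.
- The limitations paragraph of the Discussion warns of low power for the secondary outcomes only.

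**The concern.** The 0.04 is in index points, whereas f is the spread of the interaction effects divided by the within-cell SD. Only an SD and an assumed course of the group difference over the four visits can turn one into the other, and the article gives neither. In the calculation as printed, replacing 0.04 by any other raw difference would leave the 50 and the 0.91 unchanged. The text names one quantity as the effect size and computes with another.

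What is at stake is how the primary result is read. Anyone taking the paragraph at face value will believe that the trial has about 90% power for a 0.04 difference. Because the stated power limitation covers only the secondary outcomes, nothing corrects that belief. A non-significant result could then be taken as evidence against an effect of 0.04.

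**Working it through.** **Inputs from the article:** f=0.25, k=2 groups, m=4 measurements, ρ=0.5, ε=0.5, α=0.05, N=50, 1:1 allocation, raw difference 0.04. **Assumed, because not given:** the index SD and the course of the group difference over time.

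**Step 1. Reproduce the stated figure.** For this G*Power test:
- λ = f²·N·m·ε/(1−ρ) = 0.0625 × 50 × 4 × 0.5/0.5 = 12.5
- df1 = (k−1)(m−1)ε = 1.5
- df2 = (N−k)(m−1)ε = 48 × 3 × 0.5 = 72
- The noncentral F gives power 0.909, which matches 0.91. N=48 gives 0.897, so 50 is the smallest even total reaching 90%.

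The software arithmetic is correct for f=0.25.

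**Step 2. Put f=0.25 in SD units.** Let d_t be the group difference at visit t and d̄ its mean over the four visits. With two equal groups the interaction effects are ±(d_t − d̄)/2, so f = ½·√[mean of (d_t − d̄)²]/SD. Write d for the largest difference:

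| Course over days 0, 30, 60, 90 | mean of (d_t − d̄)² | f | d at f=0.25 | SD at which 0.04 gives f=0.25 |
|---|---|---|---|---|
| 0, 0, d, d | 0.2500 d² | 0.2500 d/SD | 1.00 SD | 0.040 |
| 0, d, d, d | 0.1875 d² | 0.2165 d/SD | 1.15 SD | 0.035 |
| 0, d/3, 2d/3, d | 0.1389 d² | 0.1863 d/SD | 1.34 SD | 0.030 |

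The first course is the most favourable of those tried. The two-group shortcut f = d/(2·SD), which is not the stated test, would need SD = 0.04/0.5 = 0.08.

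**Step 3. Power for 0.04 at N=50, stated test, assumed SDs.**

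| SD | linear | sustained from day 30 | days 60 and 90 only |
|---|---|---|---|
| 0.05 | 49% | 61% | 74% |
| 0.08 | 22% | 28% | 36% |
| 0.10 | 15% | 19% | 25% |
| 0.15 | 10% | 11% | 13% |
| 0.20 | 8% | 8% | 10% |

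**Step 4. More favourable settings.**
- N=60 instead of 50: 18-29% at SD 0.10.
- ε=1, the covariance implied by the planned random-intercept model, at N=50: 69-93% at SD 0.05, 21-35% at 0.10, 8-11% at 0.20.
- Baseline-adjusted mean of the three later visits, 25 per arm, which is not the stated test. Its variance factor is (1+2ρ)/3 − ρ² = 0.667 − 0.25 = 0.417. Power is 99% at SD 0.05, 95% at 0.06, 77% at 0.08, 57% at 0.10, 30% at 0.15 and 19% at 0.20.

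**The case against.** The strongest defence is that this is a condensed article. It cites a source for the 0.04, and an SD or a conversion may be in that source or in a fuller protocol. A reader might infer that f=0.25 was never derived from 0.04, but the article supports only the narrower statement that no derivation is shown.

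A reader might also infer that the trial lacks the stated power for 0.04, or that it cannot tell 0.04 from zero. Both depend on an SD that the article does not report. At an SD of 0.05, power under the stated test is 49-74%. With ε=1 and the most favourable course it is 93%, and a baseline-adjusted mean of the later visits would reach 99%. The flat claim is therefore not proven.

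It is also fair that the article calls 0.04 pragmatic, limits its meaning to the population it came from, and nowhere says that a null result would exclude it. The sample size can no longer change, and neither the estimate nor the test is affected.

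What remains is that the text says 0.04 was the value used, the calculation uses another, and nothing elsewhere in the article closes the gap. At SDs of 0.10 or more, every calculation tried stays far below 91%.

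**Conclusion.** The point stands as a wrong attribution of a power figure for the primary outcome. The G*Power result itself is right. The 91% is for f=0.25, that is, a group difference of 1.00 to 1.34 SD depending on the time course. It carries over to 0.04 only if the index SD is about 0.03 to 0.04. With roughly normal scores, such an SD would put about 95% of participants within 0.06 to 0.08 of the mean. That is implausible for an index running from below 0 to 1, in adults aged 18 to 85 with two different lung diseases.

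A large shortfall for 0.04 is therefore very likely: about 15-25% power at an assumed SD of 0.10, and 8-10% at 0.20. It is not certain, because the SD is not in the article. These figures rest on the stated ρ and ε, 50 participants, and the three time courses above. Equivalently, if the SD were 0.10, the difference covered by the 91% would be 1.00 × 0.10 = 0.10 to 1.34 × 0.10 = 0.13 index points, about two and a half to three and a half times 0.04.

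**What to change.** 1. State that 50 participants give 91% power for f=0.25, and give its meaning in SD units together with the assumed time course: about 1.0 SD if the difference is present at days 60 and 90 only, 1.15 SD if sustained from day 30, 1.34 SD if linear to day 90.
2. Remove the statement that 0.04 was the effect size used. Alternatively, state the SD and time course that link it to f and recompute.
3. From the baseline index values already collected, pooled over both arms so that no group comparison is seen, compute the SD and report the detectable difference in index points.
4. Extend the power limitation in the Discussion to the primary outcome.
5. Interpret the primary result by its 95% confidence interval against 0 and 0.04, and do not read a null result as absence of a 0.04 effect.

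The cost is some rewording and one pooled SD. No extra patients are needed and the primary analysis does not change. The price is a stated power for 0.04 that will very likely look much less favourable.

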## Results

Funding and ethics approval were obtained in April 2023. Recruitment began in January 2024 and was completed in May 2026. A total of 62 participants were randomized, of whom 60 initiated follow-up and were included in the longitudinal analysis. Overall, 49 participants completed the 90-day follow-up. Data collection has been completed, and data analysis is ongoing. The results are expected to be submitted for publication in the first half of 2027.

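### Thirty per group does not cover the stated 20% dropout: it leaves 48 participants, not the required 50, though the practical loss of power is minor

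*Protocol article*

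**What the plan says.** All of the sizing is in the protocol article, Statistical Analysis.

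- Method: "The calculation was performed using G*Power software (*F* tests: ANOVA, repeated measures, within-between interaction".
- Effect size and error rates: "The calculation assumed an effect size of *f*=0.25, a 2-sided α level of .05, and a statistical power of 90% (β=.10".
- Design inputs: "The design included 2 groups and 4 repeated measurements, with a correlation among repeated measures of 0.5 and a nonsphericity correction (ε) of 0.5".
- Result: "the required sample size was 50 participants (25 per group), with an achieved power of 0.91".
- Dropout allowance: "Considering an anticipated dropout rate of 20%, the final target sample size was increased to 30 participants per group to preserve statistical power". The sentence goes on to place this in an intention-to-treat setting. The formula for the allowance is not given.

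Allocation is 1:1 (Randomization and Blinding). The primary analysis is a linear mixed model on a modified intention-to-treat set, described as "including randomized participants who initiated follow-up and contributed data to the longitudinal analysis, regardless of adherence status".

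The Results section reports 62 randomized, of whom 60 started follow-up and were analysed. It adds: "Overall, 49 participants completed the 90-day follow-up".

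**The concern.** A dropout rate is a fraction of those enrolled. An allowance for it must therefore divide the required number by the fraction expected to remain. The target of 30 per group does not do that: with the anticipated 20% loss, fewer participants remain than the same paragraph says are needed.

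What is at stake is whether the sample-size justification is true as stated. The paragraph says that 30 per group preserves the power just quoted, and a reader can show from its own figures that at 20% loss it does not quite do so. Results are still to be submitted, so the sentence could be repeated in the results paper unless it is corrected.

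**Working it through.** **Inputs** (all from Statistical Analysis): f = 0.25, α = 0.05, k = 2 groups, m = 4 measurements, ρ = 0.5, ε = 0.5, target power 0.90, required N = 50, dropout d = 0.20, target 30 per group.

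**Step 1. Reproduce the stated power.** For the G*Power within-between interaction:

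- λ = f² · N · m · ε / (1 − ρ)
- df1 = (k − 1)(m − 1)ε
- df2 = (N − k)(m − 1)ε
- power = probability that a noncentral F(df1, df2, λ) exceeds the 5% critical value

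At N = 50: λ = 0.0625 × 50 × 4 × 0.5 / 0.5 = 12.5, df1 = 1 × 3 × 0.5 = 1.5 and df2 = 48 × 3 × 0.5 = 72. Power is 0.9089, which agrees with the stated 0.91. Fifty is also the smallest even N that reaches 0.90. The inputs and the formula are therefore not in doubt.

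**Step 2. Check the dropout allowance.**

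- Division by the fraction remaining: 25 / (1 − 0.20) = 31.25, so 32 per group, 64 in total.
- Multiplication by one plus the dropout rate: 25 × 1.20 = 30, the stated target.
- What 30 per group leaves at 20% loss: 30 × 0.80 = 24 per group, 48 in total.
- What loss 30 per group can absorb: (30 − 25) / 30 = 5/30 = 16.7%.

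**Step 3. Power at the resulting numbers**, with df1 = 1.5 throughout:

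| Participants with complete data | λ | df2 | Power |
|---|---|---|---|
| 48 (60 less 20%) | 12.00 | 69.0 | 0.8965 |
| 49 (reported completers) | 12.25 | 70.5 | 0.9029 |
| 50 (stated requirement) | 12.50 | 72.0 | 0.9089 |
| 60 (no loss) | 15.00 | 87.0 | 0.9528 |

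The value at 49 is approximate, because 49 cannot be split equally. At 48, power is 0.90 − 0.8965 = 0.0035 below target, and 0.9089 − 0.8965 = 0.0124 below the value at 50.

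**Step 4. Allow for partial data.** The figures in Step 3 count only participants with all four measurements, whereas the planned mixed model keeps whatever a participant contributed. As an approximation, assume that all 60 give baseline data, that the correlation is 0.5 between every pair of visits, and that 12 participants (6 per group) are lost straight after baseline. The effective N is 60 times the ratio of the mixed-model information on the interaction with these losses to that with complete data. It is then put into the power formula of Step 1.

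| Assumed shape of the group difference | Effective N | Power |
|---|---|---|
| Grows linearly over follow-up | 50.3 | 0.911 |
| Present in full from day 30 | 51.9 | 0.919 |
| Appears only at day 90 | 48.4 | 0.899 |

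Later dropout raises these values. For the day-90-only shape they still reach only 48.6 and 0.900. Of the three shapes tried, that is the least favourable.

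**The case against.** The strongest objection is that completers are not the analysis set. The primary analysis is a mixed model on everyone who started follow-up and contributed data, with assessments at baseline and days 30, 60 and 90. Step 4 shows that under two of the three effect shapes tried, power stays above 0.90 even if all dropouts leave straight after baseline. This stands, and it limits the consequence: a completer-only figure just under 90% does not establish that the planned analysis falls short. It does not rescue the sentence. The paragraph sized the trial on participants with four measurements and added an allowance to protect that number, and 48 is not 50. Nor can partial data help for anyone who never starts follow-up, because the analysis set leaves them out.

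Two stronger readings are tempting, and the documents do not support them.

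- A reader might infer that the trial missed its power target because 49 completed. On the plan's own formula, 49 gives about 0.903, above 0.90. Fifty is the smallest even number that meets the target, not the smallest number.
- A reader might set a loss of 13/62 = 21.0% against the 16.7% tolerance. That mixes denominators, since 16.7% is based on 60. Among the 60 who started, the loss was 11/60 = 18.3%, under the anticipated 20%. On 62 randomized, the tolerance would be 12/62 = 19.4%.

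It is also fair to object that the multiplication by 1.20 is an inference. It fits the figure exactly and division by 0.80 does not, but the point does not depend on it: 60 × 0.80 = 48 whatever the route.

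**Conclusion.** The dropout allowance is wrong as written. At the stated 20% loss, 30 per group leaves 48 participants, two fewer than the stated requirement; 32 per group (64) would have been needed. Completer-only power at that loss is 0.897, about 0.35 percentage points under the 90% target and 1.2 points under the 0.909 at N = 50. These values rest on the plan's own f = 0.25, ρ = 0.5 and ε = 0.5, and on a repeated-measures ANOVA in complete cases. Because the mixed model uses partial data, 0.897 is conservative for the planned analysis. This is a minor error in the justification and does not undermine the trial's design or its forthcoming analysis.

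**What to change.** Replace the dropout sentence, or give this wording when the sample size is described in the results paper:

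> The target of 30 per group allows for 16.7% loss (5 of 30). A 20% loss would have required 32 per group (64 in total). With 30 per group and 20% loss, 48 participants would complete, and completer-only power would be about 0.897 for f = 0.25. The mixed model also retains partial data from participants who drop out, so this figure is conservative.

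The cost is one sentence and a very slightly less favourable power statement. No further enrolment is needed, and the analysis does not change. The correction should not add a power figure for the 49 observed completers.
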